### Different trial designs

We describe two categories of possible trial designs (Figure 1).

**Figure 1. fig1-17407745221110880:**
[figure not shown]
The MARV vaccine trial coordination of different designs into a platform trial with a single steering committee and data monitoring committee.

Individually randomized in high-risk populations or during outbreaks
High-risk populationSimple individual randomization to vaccine or placebo/control in areas of high risk of exposure to MARV, including populations living near the proposed reservoirs (e.g. miners exposed to bat caves, surrounding population where outbreak is occurring). The vaccine and comparator will be delivered according to a common vaccination schedule.Transmission clusters during outbreaksSimple individual randomization to vaccine or comparator within clusters of infection transmission.
Clusters will be rings, that is, a cluster will be contacts of an index case and contacts of those contacts.Clusters will be transmission units such as households, compounds, or other types of contact structures.Cluster-randomized during outbreaks

Clusters themselves, defined as above in 1b (i) and 1b (ii) would be the unit of randomization; hence, all participants within a cluster would receive vaccine or all would receive the comparator.

Design category 1 is individual randomization, but design 1.a. does not involve transmission clusters, while design 1.b. involves relatively small (e.g. 100 or fewer people) clusters. Although the basic forms of statistical analysis for designs 1 and 2 are similar, there are subtle differences that need to be considered. For the individually randomized design, vaccines could be site-specific or even participant-specific. In the analysis of each vaccine, we include all participants who were randomized to either that vaccine or placebo/comparator and who were eligible for both at their randomization. The overall platform trial will be a blending of these designs in a sequential and non-overlapping way. For the cluster-randomized designs, 1.b. and 2, every effort will be made to ensure that the clusters are non-overlapping and geographically separate to avoid the potential for contamination.^
11
^

In some cases, it would be possible to use study design 1.a. to assess the VE against infection by recruiting cohorts of people with potential high exposure, for example, individuals having frequent contact with Rousettus bats in caves. It will take a long time to accrue events in design 1.a., but much faster for design 1.b. during outbreaks. By combining these two approaches, we will shorten the trial as much as possible. Although individual randomization is preferred, we will be able to take advantage of cluster randomization when it occurs in design 2.

## Results

### VE analysis

The primary efficacy endpoint will be analysed as a time-to-event outcome, including only those events that occur 10 days after the final vaccination dose. Such a gap of 10 days is chosen to allow time for the vaccination series to take effect and to reduce the chance of including events occurred prior to the vaccination due of the incubation period for Marburg. All participant-level failure (diagnosis with disease) and censoring events are reported relative to the time of randomization. The time of virologically confirmed (i.e. laboratory-confirmed) MARV disease is the earliest time of reported qualifying MARV disease symptoms that occur within 10 days of virological confirmation of MARV infection. Participants’ follow-up times will be right censored at the time of last contact at which endpoint status was assessed. Cox proportional hazards regression will be used for analysis. VE, measured by one minus the hazard ratio (vaccine versus placebo/comparator), will be the effect measure. Inference will be based on a one-sided logrank test of H_0_
^benefit^: VE ≤ 0.30, using an O'Brien-Fleming boundary for early termination that preserves an experimental (one-sided) 0.025 error rate; the alpha levels would be one-sided 0.0003 at 50 events and one-sided 0.0069 at 100 endpoints, where the remainder of the (one-sided) 0.025 error rate would be spent at the final analysis. Using these O'Brien-Fleming criteria after 50 and 100 events, benefit is established when estimated VE is ≥80% and ≥59%, and lack of benefit, that is, ruling out the target VE of 60% for which the trial has 90% power, is established when estimated VE is ≤−6% and ≤34%, respectively. When estimating VE against infection, the outcome would be infection as measured by time to seroconversion, using interval censoring methods for the estimand. In this case, the operating characteristics of the statistics would be the same as described above.

The choice of estimand will be fully pre-specified, according to the International Council for Harmonization guidelines.^12,13^ The treatment policy estimand, based on the Intention-To-Treat principle, would provide particularly appealing properties, given its unique capability of preserving integrity of randomization, enhanced clinical relevance due to its unconditional nature, and proper evaluation of the vaccine in the context of a regimen. A variation to be considered, consistent with common practice in vaccine evaluation, would be to include only those events that occur after a specified post-vaccination period.

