## Methods

### Operating characteristics of the trial design

A core protocol approach will be used, allowing multiple vaccine candidates to be tested against a shared placebo/control group. The primary objective of the trial will be to evaluate the effect of each vaccine on the rate of virologically confirmed MARV disease, regardless of severity. In some cases, it may also be possible to evaluated MARV infection as a co-primary outcome. Although the study may lack power for formal statistical inference about VE against severe disease or death due to MARV disease, these secondary endpoints will be evaluated and reported for each vaccine. Additional exploratory endpoints will include VE between the first and second dose, for two-dose vaccines. Infecting viruses will be sequenced as much as possible to assess the influence of virus clades and evolution on transmissibility, virulence and VE. A subset of trial participants will provide periodic blood samples. Immune markers measured from participants in this immunogenicity subset will be used to assess immune correlates of risk and protection, and help with the assessment of VE against infection.

The trial is endpoint-driven, as the main analysis for each vaccine arm versus the concurrent shared placebo/control arm is triggered by the occurrence of a total of 150 cases of MARV disease across these two arms. While results from the main analysis will be reported, blinded follow-up will continue to evaluate safety and duration of immunity. This fixed number of 150 endpoints provides 90% power to rule out the hypothesis that VE is ≤ 30%, when the true VE is ≥ 60%, where statistical significance would be achieved if the estimated VE were ≥ 50%. In the setting of COVID-19 vaccines, such results would meet or exceed the World Health Organization-Food and Drug Administration (FDA) established threshold for worthwhile VE.

A global data monitoring committee will regularly review the accumulating safety results and major endpoint results. Different candidate vaccines may be available or suitable to enter the trial at different calendar times. Using a shared placebo/control group and a common core protocol to evaluate multiple candidate vaccines in the trial, resources allocated to the evaluation of each candidate vaccine will be judiciously saved while a high standard of scientific rigour and efficiency is ensured.^
10

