^ Participants will be randomized to one of the vaccines (k in number) for which they are eligible or to one of the placebos that correspond (in appearance, dosing interval, and route of administration) to each of those vaccines. The randomization ratio will ensure that participants have the same chance of receiving a placebo (with probability 1/(k + 1) for placebo in aggregate, which is the sum of the probabilities 1/k(k + 1) for each individual placebo) as they have of receiving each individual vaccine (with probability 1/(k + 1)) for which they are eligible. Outcomes in recipients of each vaccine candidate will be compared with outcomes in all placebo recipients who were eligible to be randomized to that vaccine. This approach preserves blinding and enables comparison of each vaccine’s results directly to results from an equal number of controls who received placebo at the same time and place. Groups of sites in specific countries or subsets of sites across countries may want to collaborate in making further measurements or observations. These could be thought of as Phase 2b trials nested within the Phase 3 trial, provided that they also collect all information needed for the Phase 3 trial. Well-organized additional research studies could be conducted to assess additional secondary and supportive endpoints, such as infection or viral load (as a surrogate for transmission); nonetheless, they are not core requirements for all sites. For cluster-randomized designs, both indirect and overall vaccine effectiveness can be estimated as additional exploratory endpoints.

The trials will be double-blind to the extent possible. The best comparators will be either vaccine placebos or active comparator vaccines that are not related to protection from MARV infection, but would provide benefit to the population, for example, hepatitis A vaccine; however, a vaccine comparator could complicate safety assessments. If neither is possible, then observation-only or delayed vaccination may be used for this purpose.

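### Counting events only from 10 days after the final dose, while pooling controls across placebo schedules, can compare the arms over different periods and shift VE either way

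*Protocol article*

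**What the plan says.** The article fixes three things that meet in the primary comparison.

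- **Counting window and clock** (VE analysis). The primary endpoint is analysed by "including only those events that occur 10 days after the final vaccination dose". The time origin is separate: "All participant-level failure (diagnosis with disease) and censoring events are reported relative to the time of randomization". The section does not say when a participant enters the risk set.
- **Control group** (Operating characteristics of the trial design). Participants are randomised to a vaccine or to "one of the placebos that correspond (in appearance, dosing interval, and route of administration) to each of those vaccines". Each vaccine's outcomes are then "compared with outcomes in all placebo recipients who were eligible to be randomized to that vaccine". If neither a placebo nor an active comparator is possible, "then observation-only or delayed vaccination may be used for this purpose".
- **Schedules.** The same section lists "VE between the first and second dose, for two-dose vaccines" as an exploratory endpoint, so two-dose vaccines are foreseen. No dosing interval is given. In the Figure 1 text, design 1.a carries the statement "The vaccine and comparator will be delivered according to a common vaccination schedule"; the other designs have no such statement.

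The estimand paragraph in VE analysis favours a treatment-policy estimand on the intention-to-treat principle. It calls a post-vaccination window a variation to be considered, although the paragraph before it already adopts one.

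**The concern.** The window is tied to a participant's own final dose, and that day depends on the schedule. Suppose a one-dose and a two-dose vaccine are offered to the same participants. Recipients of the two-dose vaccine have events counted only after dose 2 plus 10 days, while the part of their control pool on the one-dose placebo is counted from day 10. For the one-dose vaccine the mismatch runs the other way.

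Observation-only controls have no final dose, so the rule gives them no start day. Delayed-vaccination controls have one, but it is not comparable with that of the vaccine arm.

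At stake are both error rates of the pairwise test. A longer-schedule vaccine at the 30% null could pass too often, and a good shorter-schedule vaccine could fail too often. Either result would undercut the stated purpose of the shared controls, which is to compare each vaccine with controls from the same time and place.

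**Working it through.** **Inputs from the article:** 150 events, equal allocation, one-sided 0.025, null VE 30%, target VE 60% with 90% power, success at estimated VE of about 50%, and Table 1.

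**Assumptions (not in the article):** one one-dose and one two-dose vaccine offered concurrently; dose 2 on day 28; control pool split 50/50 between the two placebos; constant hazard; everyone at risk from randomisation with early events not counted. Dropout and the interim looks are ignored.

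**Step 1: reproduce the plan's figure.** With hazard ratio h and 150 events, the standard error of the log hazard ratio is s(h) = √(1/d₁ + 1/d₀), where d₁ = 150h/(1+h) and d₀ = 150/(1+h).

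- s(0.7) = 0.166 and s(0.4) = 0.181.
- Chance of rejecting: Φ{[ln(0.7/h) − 1.96·s(0.7)] / s(h)}.
- At h = 0.4: Φ[(0.560 − 0.325)/0.181] = 90%. At h = 0.7: 2.5%.
- Critical VE: 1 − 0.7·exp(−0.325) = 49%.

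This agrees with the stated 90% power and 50% threshold.

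**Step 2: mean follow-up.** From Table 1, mean follow-up F = final analysis time − ½ × (total participants ÷ accrual rate), at 30.44 days per month. For 30,000/month: 4.2 − ½ × 1.20 = 3.6 months, about 110 days. For 1,000/month: 16.7 − ½ × 13.72 = 9.84 months, about 299 days.

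**Step 3: observed hazard ratio.** For rare events, observed HR = true HR × (F − w_vaccine) / mean(F − w_control), where w is 10 days (one dose) or 38 days (two doses). At F = 110:

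- Two-dose, true VE 30%: 0.7 × 72/86 = 0.586, so VE reads 41%.
- One-dose, true VE 60%: 0.4 × 100/86 = 0.465, so VE reads 53–54%.

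**Step 4: all rows of Table 1.**

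| Accrual/month | F (days) | Two-dose, true 30%: VE reads | One-sided error | One-dose, true 60%: VE reads | Power |
|---|---|---|---|---|---|
| 1,000 | 299 | 34% | 5% | 58% | 85% |
| 5,000 | 163 | 37% | 9.5% | 56% | 78% |
| 10,000 | 135 | 39% | 13% | 55% | 74% |
| 20,000 | 117 | 40% | 17% | 54% | 70% |
| 30,000 | 110 | 41% | 19% | 53–54% | 68% |

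**Step 5: vary the assumptions.**

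- 14-day gap, F = 110: 0.7 × 86/93 = 0.647, error about 7%.
- 28-day gap, F = 365: 0.7 × 327/341 = 0.671, error about 4.5%.
- Observation-only controls counted from day 0, F = 110: true VE 30% reads 36% for one dose (0.7 × 100/110) and 54% for two doses (0.7 × 72/110).
- Risk concentrated soon after randomisation (hazard declining with mean 60 days, 182 days of follow-up, 28-day gap): true VE 30% reads about 47% for the two-dose vaccine. By exact binomial calculation, the chance of an estimate of at least 50% is 41.5%, against 3.0% with equal windows.

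**Step 6: what removes it.** Cox simulation (18,062 per arm, 1% attack rate over 182 days, 28-day gap) gave these results for the two-dose vaccine. One common start day returned 28–29% for a true 30%, and 60% for a true 60%. Delayed entry on the randomisation clock returned 30–31% and 60%. Restarting the clock at each participant's own start works only if the hazard is constant; with the declining hazard a true 30% still reads about 47%.

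**The case against.** The strongest reply is that the bias is conditional. The article does not say that participants are at risk from randomisation while their early events go uncounted. Delayed entry fits its wording, removes the bias under proportional hazards, and is a detail that a fuller protocol or analysis plan could hold. The mismatch also needs concurrent vaccines with different schedules and overlapping eligibility, whereas vaccines may be site-specific. The estimand paragraph leaves the window open. All of this stands, so a reader who infers that VE is biased in every comparison goes beyond the text. What remains is that the article itself fixes the window, the clock and the control pool, and followed literally these compare unequal periods.

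The common-schedule statement does not settle the matter. It is made for design 1.a only, may mean a vaccine and its own comparator, and sits beside placebos with differing intervals.

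Two stronger readings are tempting but unsupported:

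- **That participants who never reach the final dose are dropped.** The rule restricts events, not participants. The section Different trial designs includes everyone randomised to the vaccine or comparator who was eligible for both. Handling of incomplete series is unstated.
- **That delayed-vaccination controls are meant to count only after their own vaccination.** That would defeat the comparison, and these controls are only a fallback. The fair criticism is that the window is not usably defined for them.

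Finally, the 19% error belongs to the shortest follow-up in Table 1 and should not be quoted alone.

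**Conclusion.** The point holds in conditional form. Where vaccines with different schedules share controls and early events are merely left uncounted, the stated rules overstate VE for the longer schedule and understate it for the shorter. Across Table 1, with a 28-day gap, an even placebo split and constant hazard, the one-sided error is about 5–19% for the two-dose vaccine and power about 85–68% for the one-dose vaccine. A shorter gap or longer follow-up shrinks the effect; early-concentrated risk, which is plausible in rings around an index case, enlarges it. The gap, split and hazard shape are assumptions, because the article gives none. A single vaccine with its matched placebo, or vaccines on identical schedules, is unaffected.

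Separately, and without any assumption, the window has no usable definition for observation-only or delayed-vaccination controls, and the two paragraphs of VE analysis disagree on whether the window is adopted or only under consideration.

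**What to change.** In each pairwise comparison, start counting in both arms on the same day after randomisation: the scheduled final-dose day of the vaccine under test plus 10 days. Use delayed entry on that day. Apply it to all concurrent eligible controls, whatever their placebo schedule or non-vaccinated comparator, and regardless of doses received. Reconcile the window in VE analysis with the estimand paragraph that follows it, and report the analysis of all events from randomisation (intention-to-treat) beside it.

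The cost is a change of analysis wording. Some early control events on shorter placebo schedules would no longer count towards the 150 for a longer-schedule vaccine, so that comparison may reach its target somewhat later.

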### Study sample size for individually randomized designs

The trial is endpoint-driven, as the primary analysis for each vaccine arm versus the concurrent shared placebo/control arm is triggered by occurrence of a total of 150 cases of MARV disease across these two arms. The primary analysis results will be reported but blinded follow-up will still continue. We assume a 1% cumulative attack rate in the control arm over 6 months of outbreak time. The trial period could involve several years of follow-up and across outbreaks. As stated above, there will be two interim analyses at the points when 1/3 and 2/3 of events have occurred, respectively. We use the O'Brien-Fleming-type spending function for both false-positive and false-negative errors. All the sample size calculations were conducted using the R package *rpact*.

For example, with a target level VE of 60%, with 150 total endpoints in a pairwise comparison, there is approximately 90% power to reject VE less than or equal to 30% if true VE is 60%, based on a logrank test with one-sided type I error rate of 0.025. With equal allocation to the active vaccine arm and the control arm, a minimum follow-up of 3 months for the last accrued participant and an annual drop rate of 10%, we calculated sample sizes for different accrual rates (Table 1). If on average 30,000 participants will be accrued each month, we need 18,062 participants per arm and an expected study duration of 9.1 months. Lower accrual rates are associated with longer study durations but smaller sample sizes. Using the sample size of 18,062 per arm, we simulated 100 times exponentially distributed event times without early stopping to investigate the coverage of the two-sided confidence interval of the VE estimate. The average total number of events is 179 and the average 95% confidence interval for the VE is (45%, 71%). The lower confidence bound would exclude 30% with a probability of 0.93, and the point VE estimate is greater than 50% with a probability of 0.91. We performed a sensitivity analysis, varying the accrual rate, assuming a 1% cumulative attack rate in the control arm over a 12-month period with an annual dropout rate of 10%, and a minimum follow-up of 6 months after the last accrual (Table 1). The sample size increases with increasing accrual rate to about 18,062 participants per arm. The best sample size is about 20,000 participants per arm, or about 40,000 participants per vaccine/comparator combination.

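### One 10-day window both links symptoms to virological confirmation and dates the event, so a case confirmed late can be misdated, moved past the post-dose gap, or left without an event time

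*Protocol article*

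**What the plan says.** All the relevant rules are in the protocol article, Results, VE analysis.

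- **Event time.** The time of virologically confirmed disease is "the earliest time of reported qualifying MARV disease symptoms that occur within 10 days of virological confirmation of MARV infection".
- **Counting rule.** The primary endpoint is analysed "including only those events that occur 10 days after the final vaccination dose".
- **Purpose of the gap.** Besides giving the vaccine time to act, the gap is meant "to reduce the chance of including events occurred prior to the vaccination due of the incubation period for Marburg".
- **Time origin and label.** "All participant-level failure (diagnosis with disease) and censoring events are reported relative to the time of randomization". Here the failure is called a diagnosis; the next sentence dates it by symptoms.
- **Effect measure.** "VE, measured by one minus the hazard ratio (vaccine versus placebo/comparator), will be the effect measure".

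No sentence says what happens when the first symptom came more than 10 days before confirmation. Nor does any sentence say whether the confirmation date is the day the specimen was taken or the day the result was reported. The paragraph that follows leaves the choice of estimand to pre-specification and does not alter the dating rule.

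**The concern.** A symptom-to-test window is a sensible way to attribute an illness to Marburg virus. The difficulty is that the same window also limits where the onset date is looked for. If confirmation comes more than 10 days after the first symptom, that symptom is outside the set searched. Either a later symptom within the window becomes the event date, or none exists and a confirmed case has no event time.

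Two things are at stake. First, an illness that began inside the post-dose gap can be dated after it and counted, so laboratory timing rather than the illness decides whether the case enters the primary analysis. Second, genuine confirmed cases may not count towards the 50, 100 and 150 events that trigger the analyses.

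**Working it through.** **1. The plan's own figure.** The concern does not dispute the power statement, but the statement sets the scale. Under Study sample size for individually randomized designs, 150 events give about 90% power to reject VE ≤ 30% when true VE is 60%, one-sided 0.025, equal allocation. Hazard ratio relative to the null: 0.40/0.70 = 0.571.

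- Freedman: √150 × (1 − 0.571)/(1 + 0.571) − 1.96 = 1.38, power 0.916.
- Exact conditional binomial (49 or fewer of 150 events in the vaccine arm): power 0.884.
- Schoenfeld: (√150/2) × ln(1/0.571) − 1.96 = 1.47, power 0.929.

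The stated figure is reproduced.

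**2. The rule applied literally.** Days are counted from the final dose; an event counts if dated after day 10.

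| Symptom days | Confirmed | First symptom | Date under the rule | Result |
|---|---|---|---|---|
| 6, 9, 12 | 15 | 6 | 6 | excluded, as intended |
| 6, 9, 12 | 20 | 6 | 12 | counted, though onset was in the gap |
| 14, 18 | 26 | 14 | 18 | counted, dated 4 days late |
| 14 only | 26 | 14 | none | no event time |

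The first two rows are the same illness. Only the confirmation day differs.

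**3. How often this could happen.** The document gives no delays. Assumption, for illustration only: onset-to-confirmation delay is gamma with shape 2.

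| Mean delay (days) | 3 | 4 | 6 | 8 |
|---|---|---|---|---|
| P(delay > 10) | 0.010 | 0.040 | 0.155 | 0.287 |
| q | 0.0017 | 0.0093 | 0.054 | 0.129 |

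Here q is the share of in-gap onsets re-dated past day 10: the average of P(delay > 20 − u) over onset day u uniform on 0 to 10. It assumes symptoms are reported every day up to confirmation. A patient whose symptoms ended before the window opened would be dropped instead of moved.

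**4. Effect on VE when cases are moved.** Let r be the number of in-gap cases per arm divided by the number of later control cases, and take VE = 0 in moved cases. With true VE 60%:

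estimated VE = 1 − (0.4 + r·q)/(1 + r·q).

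For the individually randomized design, the sample-size section uses exponential event times and at least 3 months of follow-up, about 91 days. Then r is at most about 10/(91 − 10) = 10/81 = 0.12, treating follow-up as starting at the final dose.

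| Mean delay (days) | 4 | 6 | 8 |
|---|---|---|---|
| r = 0.12 | 59.9% | 59.6% | 59.1% |
| r = 1 | 59.4% | 56.9% | 53.1% |

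The row r = 1 means as many cases in the 10-day gap as in all later control follow-up. At most it describes rings, where onsets may crowd soon after enrolment. At a mean delay of 3 days the estimate is 59.9% even with r = 1.

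**5. Effect on power.** Suppose a share f of the 150 counted events are moved cases with VE = 0, split equally between arms. At f = 5%, the vaccine arm has 142.5 × 0.4/1.4 + 3.75 = 44.5 events and the control arm 105.5, so VE is 57.9%. Schoenfeld power by f (0.929 at f = 0):

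| f | 1% | 5% | 10% | 15% |
|---|---|---|---|---|
| Estimated VE | 59.6% | 57.9% | 55.7% | 53.4% |
| Power | 0.92 | 0.87 | 0.80 | 0.70 |

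These shares are assumed. For comparison, step 4 implies f = 2rq/(1.4 + 2rq). With r = 0.12 and a mean delay of 8 days that is 0.031/1.431, about 2%.

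**6. Effect when cases are dropped.** If late-confirmed cases are lost equally in both arms, VE is not biased. Reaching 150 counted events then takes 150/0.95 = 158 true cases at 5% loss and 150/0.85 = 176 at 15%.

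**The case against.** **The window may be meant for linkage only.** On that reading, 10 days ties an illness to a positive test and the event keeps its true first symptom. This would remove the problem and is probably near the intent. But the sentence takes the earliest among symptoms lying within the window, and nothing nearby restores an earlier onset. Sites working across several outbreaks and years could apply it differently. The objection lowers the severity without closing the gap.

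**Confirmation may mean the specimen date.** A reader might infer that fatal cases are lost: onset day 14, death day 20, result day 32. That holds only if the report date is meant. With a specimen taken on day 20, onset is 6 days earlier and the case is counted and correctly dated. The article does not settle this, so the loss is possible but not shown. Late presentation would remain a problem on either meaning.

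**Upward bias.** A reader might also infer inflated VE. If mean delay were 4 days in controls and 6 in vaccinees, and all cases outside the window were dropped, a true 60% would read 1 − 0.4 × 0.845/0.960 = 65%, and a true 30% would read 38%. No part of the document gives such a difference between arms. Operating characteristics of the trial design makes the trial double-blind as far as possible, and allows observation-only or delayed vaccination only if neither placebo nor an active comparator can be used. The mechanism exists for those comparators; the bias is not established.

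**Zero efficacy in moved cases is extreme.** The gap runs from the final dose, and the article plans to explore VE between doses, so two-dose recipients may already be partly protected. With VE of 30% in moved cases, a 10% share gives 57.5% and power 0.86, against 55.7% and 0.80. This objection stands, and the figures in steps 4 and 5 should be read accordingly.

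**The estimand is still open.** Under a treatment-policy analysis with no post-dose gap, crossing the gap would not matter. Late dating and lost cases would remain.

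**Conclusion.** The point holds in limited form. As worded, the rule can misdate a case confirmed more than 10 days after first symptom, move an in-gap onset into the primary analysis, or leave a confirmed case without an event time. That follows from the text and needs no assumption about delays.

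The size is unknown, because it depends on confirmation delays and on the meaning of the confirmation date. Under the gamma delays assumed here and the article's exponential event times, the shift is probably under 1 VE point in the individually randomized design. It could reach several points only in rings with slow confirmation, and it is negligible where confirmation is prompt. Moved cases dilute VE towards zero, which works against the vaccine and does not make rejecting VE ≤ 30% easier. Dropped cases cost waiting time if the loss is equal between arms. Upward bias would need delays that differ by arm, which the document does not show. Severity is minor to moderate.

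**What to change.** Separate the two jobs of the window in the endpoint definition:

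1. **Qualify the case.** Require qualifying symptoms within 10 days of collection of the MARV-positive specimen, post-mortem specimens included. The anchor is the collection date, not the report date.
2. **Date the event.** Use the first qualifying symptom of that same illness, even if it precedes the window.
3. **Apply the gap.** Apply the 10-days-after-final-dose rule to that onset date.

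The window should stay as the attribution criterion. Dropping any limit on the interval between symptoms and specimen would give up attribution and is not clearly better.

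The cost is a change to one sentence of the definition, using onset and collection dates that case investigation would normally record. The small downside is that an unrelated earlier symptom may occasionally set onset slightly early; blinded endpoint review can resolve this.
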